#### Nutrition

Usual dietary intake is assessed using the Food Frequency Questionnaire-Revised (FFQ-R), a widely used and empirically validated tool for estimating habitual dietary intake (Thompson and Subar, 2013). Studies demonstrate its reliability, with test-retest correlations ranging from 0.70 to 0.85, and its validity through significant correlations with both dietary records (*r* > 0.50) and biomarkers such as plasma carotenoids and urinary nitrogen (Subar et al., 2001; Thompson and Subar, 2013; Willett et al., 1985). The FFQ-R is a robust method for efficiently capturing dietary patterns in large-scale studies.

#### Sleep

The Pittsburgh Sleep Quality Index (PSQI) is a self-report survey with 19 items (Buysse et al., 1989) to assess sleep quality and quantity, sleep disturbances, typical time in bed, and sleep efficiency in the past 4 weeks. Responses are used to determine a global score that ranges from 0 to 21, with higher values representing worse sleep quality (5 or greater represents impaired sleep quality). Studies have indicated high sensitivity and specificity for the PSQI in predicting insomnia, high internal consistency, and high test-retest reliability and convergent validity with other sleep measures (Backhaus et al., 2002; Cole et al., 2006).

#### Stress

The Weekly Stress Inventory Short Form (WSI) will be administered to measure self-reported stress. The WSI is a 25-item list of events usually perceived as stressful (Brantley et al., 2007). If the event occurred, participants rate on a 7-pt Likert-type scale the amount of stress caused by the event. The WSI has been found to have adequate internal consistency, reliability, and validity (Brantley et al., 2007).

#### PTSD symptoms

The Posttraumatic Stress Checklist 5th edition (PCL-5) is a 20-item self-report measure that assesses the 20 DSM-5 symptoms of PTSD (Weathers et al., 2013). We will use the version with the Life Events Checklist for DSM-5 (LEC-5) and extended Criterion A component to permit the assessment of trauma events and an index event. Items are rated on a 5-point scale ranging from 0 (not at all) to 4 (extremely) over the past 30 days (Weathers et al., 2013). Good internal reliability, convergent validity with the CAPS, and diagnostic efficiency of the PCL have been demonstrated across trauma populations (Blevins et al., 2015; Wortmann et al., 2016).

#### Substance abuse

The Alcohol Use Disorders Identification Test (AUDIT), a 10-item self-report screening questionnaire, is used to assess alcohol consumption, drinking behaviors, and alcohol-related problems (Barry and Fleming, 1993). The AUDIT demonstrates good reliability and validity across various populations; studies report high internal consistency, with Cronbach's alpha ranging from 0.77 to 0.86 (Barry and Fleming, 1993; Campo-Arias et al., 2013; Daeppen et al., 2000; Zavar et al., 2015). Test-retest reliability is also strong, with correlation coefficients between 0.71 and 0.95 (Daeppen et al., 2000; Zavar et al., 2015). The AUDIT also shows good construct validity, with factor analyses supporting a two-dimensional structure (Campo-Arias et al., 2013; Zavar et al., 2015).

#### Anxiety sensitivity

The Anxiety Sensitivity Index-3 (ASI-3; Taylor et al., 2007) is an 18-item self-report used to assess concern associated with possible negative consequences of anxiety-related symptoms (e.g., “It scares me when my heart beats rapidly”). The scale includes some items from the original ASI (Reiss et al., 1986). Factor analyses consistently support a three-factor structure comprising physical, cognitive, and social concerns (Farris et al., 2015; Kemper et al., 2012; Lim and Kim, 2012; Wang, 2014). The ASI-3 shows good internal consistency, test-retest reliability, and construct validity in various populations, including clinical and non-clinical samples (Farris et al., 2015; Wang, 2014).

#### Experiential avoidance

The Acceptance and Action Questionnaire-II (AAQ-II) is a self-report psychological measure used to assess an individual's level of psychological inflexibility or experiential avoidance (Bond et al., 2011). Higher scores indicate greater levels of experiential avoidance and psychological inflexibility. The AAQ-II demonstrates strong psychometric properties across diverse populations. Multiple studies have confirmed its unidimensional structure, internal consistency, and test-retest reliability (Bond et al., 2011; Lin et al., 2023; Yavuz et al., 2016). The AAQ-II shows concurrent, predictive, and incremental validity in explaining various outcomes, including depression, anxiety, and wellbeing (Bond et al., 2011).

#### Cognitive appraisals

A cognitive appraisal questionnaire developed by Tomaka et al. (1997) is utilized as a self-report instrument designed to measure an individual's cognitive appraisals regarding a specific stressful situation from the past week. Similarly, the Stress Appraisal Measure (SAM) is a self-report instrument comprised of 28 items (Peacock and Wong, 1990); each item is rated on a 5-point Likert scale regarding how the individual feels about the specific stressful situation that was identified in the CAQ; responses range from 1 “Not at all” to 5 “Extremely.” The SAM has been validated across multiple languages and cultures, demonstrating generally satisfactory reliability and validity (Durak and Durak, 2012; Durak and Senol-Durak, 2013). Convergent and discriminant validity have been established through correlations with related measures (Durak and Senol-Durak, 2013). The SAM's ability to predict stress-related outcomes and its gender invariance have also been supported (Durak and Durak, 2012; Durak and Senol-Durak, 2013).

#### Depressive symptoms

The Beck Depression Inventory-2nd Ed. (BDI-II) is a 21-item self-report measure assessing depressive symptoms, including suicidal ideation, over the past 2 weeks (Beck et al., 1996). It demonstrates high reliability, with internal consistency coefficients (α = 0.89–0.93) and strong test-retest reliability (*r* = 0.73–0.96) (Beck et al., 1996; Dozois et al., 1998). Its validity is supported by correlations with other depression measures, such as the Hamilton Depression Rating Scale (*r* = 0.71) and PHQ-9 (*r* = 0.67), and its sensitivity to changes in symptom severity (Beck et al., 1996).

#### Health-related self-efficacy

The Health-Specific Self-Efficacy Scales measure individuals' confidence in their ability to successfully engage in behaviors related to preventive nutrition, physical exercise, and alcohol resistance (Schwarzer and Renner, 2005). These scales are grounded in social-cognitive theory and assess perceived self-efficacy, which refers to one's belief in one's capacity to perform actions necessary to achieve desired health outcomes (Schwarzer and Renner, 2000). Each scale includes items addressing barriers to behavior change, such as managing routines or coping with stress. The scales demonstrate strong reliability, with Cronbach's alpha values of 0.87 for the nutrition scale, 0.88 for the physical exercise scale, and 0.79 for the alcohol resistance scale, indicating high internal consistency (Schwarzer and Renner, 2005). Evidence supports the scales' utility in predicting health-related intentions and behaviors, with significant correlations between self-efficacy scores and subsequent behavior changes over time (Schwarzer and Renner, 2005).

#### Demographic measures

Basic demographic information, including age, race, ethnicity, family income, marital status, and education level, is assessed by self-report.

#### Medication use

Medication use is assessed by self-report during the screening period to determine participant eligibility, ensuring that current medications do not confound study outcomes. At each lab assessment time point, participants are asked to report any changes in medication use. An open-response option is provided to capture detailed information, allowing participants to type in the names and dosages of their specific medications. This approach enables comprehensive and precise documentation of medication use across all study phases.

#### Accelerometry

Participants are provided with an Actigraph wGT3X-BT watch and instructed on its use to track accelerometer-based physical activity and sleep measures each day for 1 week following each assessment session. After the watch is returned, data are downloaded for later analysis. The wGT3X-BT is the industry standard for accelerometer monitoring of physical activity and sleep (Breteler et al., 2019; Romanzini et al., 2014). The device is small (weighing only 19 grams), unobtrusive, tamper-resistant, well-tolerated, and does not hinder activity (Breteler et al., 2019). The accompanying ActiLife software is utilized for data download and analysis.

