## Abstract

Research has indicated strong associations between posttraumatic stress and cardiovascular disease (CVD) risk. Individuals with posttraumatic stress disorder (PTSD) tend to show patterns of elevated CVD risk earlier in life than the general population. The need for developing effective interventions for CVD risk-reduction in PTSD is increasingly evident. The present paper outlines the theoretical background and methodological details for the protocol of an ongoing NHLBI-funded longitudinal study (entitled *Investigating Cardiac Health of Adults with Trauma*) to test the effects of a health behavior intervention as an adjunct to standard trauma therapy in PTSD. The health behavior intervention addresses CVD-related health behaviors (physical activity, nutrition, sleep, and stress). Participants are randomized to the health behavior intervention plus standard trauma therapy condition or a standard trauma therapy control group. Outcome assessments are conducted before and after the 12-week intervention program in the experimental group, and 12 weeks apart for the control group, as well as at 6-month and 12-month follow-up time points. The outcomes include laboratory measures of CVD risks/markers (e.g., endothelial function, arterial stiffness, lipids, blood pressure), actigraphy-based measures of physical activity and sleep, and standardized self-report measures of sleep, physical activity, nutrition, stress, and psychological functioning (e.g., PTSD symptoms, depressive symptoms). The study findings will provide valuable data on the effectiveness of the health behavior intervention in producing predicted changes in the target CVD-related behaviors/markers.

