### Measures

#### Outcome assessment sessions

Four assessment sessions provide an indication of treatment-related outcomes. These sessions are conducted in person at a University-based laboratory at our study site in Ft. Lauderdale, FL (U.S). The first assessment (baseline) is conducted prior to the first week/study onset in each condition. The second assessment (post-treatment) is conducted at the 3-month time point (after the last healthy lifestyle session in the experimental condition). The third and fourth assessments (follow-up) are conducted at the 6-month and 12-month time points. Each assessment session consists of the same outcome measures: blood pressure, lipids, body mass index (BMI), arterial stiffness, endothelial function, heart rate variability (HRV), physical activity, nutrition, perceived stress, sleep (quantity, efficiency, quality, and restfulness), and psychological measures (PTSD symptoms, depressive symptoms). Results of the lipid measures and blood pressure are reviewed with participants following each assessment, and it is recommended to those with clinically elevated levels that they consult with their primary care physician or other medical provider about such findings.

Due to potential confounding effects on lipids and/or blood pressure, participants are asked to refrain from caffeine and strenuous exercise for 3 h, and smoking for 30 min, prior to assessment sessions. These sessions are scheduled early in the morning (approx. 8:30 a.m.) due to the requirement of fasting for lipid assessment. Non-compliance with restrictions requires rescheduling. After the lipid assessment a standardized snack (granola bar, and water/juice) is provided. A doctoral research assistant (under the direction of the PI) leads each assessment session. The data collection for the assessment sessions lasts approximately 90 min. Assessment of the following variables involving physical measurement is conducted first:

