#### Health behavior/lifestyle intervention

The healthy lifestyle intervention is a 12-session program with sequential but overlapping modules for increasing physical activity, enhancing good nutrition, improving sleep, and improving stress management. The sessions are conducted individually and are held weekly for 90 min. Participants have the option of conducting the intervention sessions (health behavior and/or trauma therapy sessions) in-person or virtually via a secure HIPAA-compliant Zoom platform. The length of the program was determined by the need to be long enough to effectively address the 4 modules, while also being relatively brief to minimize burden for participants and enhance likelihood of compliance. For the current project, the decision to utilize 12 sessions was also informed by positive feedback from the participants and interventionists in the pilot study regarding the program length.

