The first module includes psychoeducation on physical activity (health benefits of physical activity and the health risks associated with physical inactivity and overweight) in session 1, as well as implementation of an exercise regimen and discussion of some of the inherent challenges. Participants are encouraged to begin a physical activity regimen that is consistent with recommendations for a healthy lifestyle (aerobic exercise at least 20 min 2–3 times per week). However, interventionists instruct participants to work toward exercise goals that can be incorporated into their lifestyles and maintained. In addition, participants walk for 20 min with the interventionist during intervention sessions 2–5. Session 2 includes discussion of healthy food choices, health risks associated with unhealthy foods, appropriate caloric intake for weight loss (as applicable), reading food labels, fat, vitamin, and sugar content, and setting dietary goals. The interventionist also helps participants distinguish diets from lifestyle changes, emphasize self-monitoring of foods, and helps participants build strategies for nutritional self-control. Nutritional recommendations include a balanced diet, enhancing consumption of fruits and vegetables, and reducing sugars, fat/saturated fat, and caloric intake (as appropriate per participant goals). During sessions 3 and 4, the participant and interventionist work together to analyze current nutritional habits and plan a healthier nutritional plan. Session 3 includes discussion of participant efforts to incorporate physical activity and healthy nutrition into their lifestyle, and the potential for social support to be helpful in behavior change. This session also addresses stress and eating. Interventionists closely monitor the stress coping skills of participants and discuss potential distress associated with giving up previously used unhealthy eating approaches to cope (especially in coping with PTSD symptoms). To address potential desire to be overweight for protection against abuse, alternative methods of achieving a sense of safety are discussed. Session 4 focuses on the skills of shopping for healthy food, planning healthy meals, and reducing behavioral cues/triggers for binge eating and unhealthy eating (e.g., storing foods out of sight, strategies for parties, special events and restaurants, managing emotions). Sessions 5 and 6 will include further discussion of progress and challenges with the physical activity and nutrition regimens.

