
The sleep-focused intervention begins in session 5 and continues into session 8. In the fifth session, an overview of common sleep problems is introduced, and the participant addresses any sleep difficulties they have had. A rationale for the treatment used in our protocol is provided. During sessions 6 through 8, cognitive behavioral strategies for assisting with sleep improvement are incorporated and discussed. In session 6, participants also identify a problematic nightmare (where applicable) and initiate the process of imagery rehearsal therapy by beginning to develop and write a modified version of the dream. In addition to discussion of insomnia treatment strategies in sessions 7 and 8, participants continue to develop their modified dream and rehearse it in session. Participants are also instructed to rehearse the modified dream daily for 5–20 min.

Sessions 9–12 focus on stress management, relapse prevention, and other issues related to termination of the program. During session 9, the interventionist provides an overview of the cognitive-behavioral model of stress and initiates a discussion of various aspects of the model (e.g., negative thoughts, negative emotions and their relationship to behavior). Between sessions 9 and 10, participants are asked to self-monitor negative thoughts to provide a basis for follow-up discussion in session 10, which focuses on common patterns of negative thoughts and associated negative feelings. During session 10, participants are also familiarized with thought logs (Beck, 2021), which use personal situations identified by participants to assist in identifying relationships between negative thoughts, negative feelings, and behavioral outcomes, as well as constructing responses to stressful situations that are more adaptive. Participants are given homework to complete two or more thought logs between sessions 10 and 11, and the results are discussed during session 11. During session 12, discussion of thought logs and stress coping is continued for the first part of the session. The last portion of the final session includes a review of the skills learned, discussion of risks for relapse and skills for relapse prevention, and discussion of any remaining concerns associated with termination of the intervention program.

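### The baseline ActiGraph week follows the baseline visit and nothing keeps the first health session out of it, so the experimental arm's baseline device activity may include on-treatment days

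*Protocol article*

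**What the plan says.** All places are in the protocol article.

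- **Device wear** (Accelerometry): the watch is used to "track accelerometer-based physical activity and sleep measures each day for 1 week following each assessment session". The baseline visit is not excepted.
- **Baseline visit** (Outcome assessment sessions): "The first assessment (baseline) is conducted prior to the first week/study onset in each condition". The visit is placed before week 1; the wear week that follows it is not mentioned.
- **Post-treatment visit** (same section): "The second assessment (post-treatment) is conducted at the 3-month time point (after the last healthy lifestyle session in the experimental condition".
- **Interval between visits** (Abstract): "Outcome assessments are conducted before and after the 12-week intervention program in the experimental group, and 12 weeks apart for the control group".
- **Programme length** (Health behavior/lifestyle intervention): "The healthy lifestyle intervention is a 12-session program with sequential but overlapping modules", and "The sessions are conducted individually and are held weekly for 90 min".
- **Content of session 1** (same section): education on physical activity, "as well as implementation of an exercise regimen and discussion of some of the inherent challenges".
- **Sleep content** (same section): "The sleep-focused intervention begins in session 5 and continues into session 8".

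The Data analysis plan analyses change by condition, with slopes from baseline to post-treatment, to 6 months and to 12 months. The Discussion presents ActiGraph monitoring as firmer ground for judging change in activity and sleep than self-report alone.

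**The concern.** A baseline should be measured before the treatment can act on it. Here the device baseline is collected after the visit that is called baseline, in a window where the first health session may already be taking place. That session is about exercise, and only the experimental arm receives it. Any early rise in activity would lift that arm's baseline and leave the control baseline alone.

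The error would enter all three planned contrasts, because each is measured from the same baseline, and later wear weeks cannot correct it. The questionnaire baseline is not exposed in this way: the IPAQ is completed at the visit and looks back over the previous week. A real effect on activity could therefore look weaker on the device than on the questionnaire, although the article treats the device as the better measure.

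**Working it through.** **The plan's own design figure.** With 81 per arm, alpha 0.05 two-sided and 80% power, a two-sample t-test detects d = 0.443. The Summary of the power section states 0.47, at which power is 84.4%. The stated figure is not reproduced exactly, but it errs on the cautious side and has no bearing on this point. The same t-test gives the power values below.

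**Calendar.** Take the baseline visit as day 0 and the wear days as days 1 to 7.

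- Session 1 to session 12: 11 × 7 = 77 days.
- The post-treatment visit comes no earlier than session 12, so the latest day for session 1 is the visit interval minus 77.
- Interval of 12 weeks: 84 − 77 = day 7, the last wear day.
- Interval of 3 months, taken as 91 days: 91 − 77 = day 14. Session 1 on days 8 to 14 leaves the wear week clean, but session 1 on days 1 to 7 is equally allowed.

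**Attenuation.** Let f be the share of the 7 wear days that are on-treatment, and e the share of the final effect already present on those days. With the control arm unaffected and the standard deviation of change unaltered,

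observed d = d × (1 − f × e).

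The document gives neither f nor e, so both are assumptions. The planned d for physical activity is 0.70 to 0.89 (Physical activity and BMI). At 81 per arm:

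| Overlap f | e | d from 0.70 (power) | d from 0.89 (power) |
|---|---|---|---|
| 0 | any | 0.70 (99%) | 0.89 (>99%) |
| 4/7 | 0.10 | 0.66 (99%) | 0.84 (>99%) |
| 4/7 | 0.25 | 0.60 (97%) | 0.76 (>99%) |
| 4/7 | 0.50 | 0.50 (89%) | 0.64 (98%) |
| 6/7 | 0.10 | 0.64 (98%) | 0.81 (>99%) |
| 6/7 | 0.25 | 0.55 (94%) | 0.70 (99%) |
| 6/7 | 0.50 | 0.40 (72%) | 0.51 (90%) |

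Example: 0.70 × (1 − 4/7 × 0.50) = 0.70 × 0.714 = 0.50.

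At the edge of the 84-day reading, session 1 on day 7 overlaps at most 1 of 7 days. With e = 0.50, d = 0.70 × (1 − 1/7 × 0.50) = 0.65, and power is 98%.

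**Later contrasts.** The shift is a fixed amount, d × f × e. With d = 0.70, f = 4/7 and e = 0.25 it is 0.10 standard deviations. It comes off all three contrasts, so it takes a larger share of any effect that has faded by 6 or 12 months.

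**The case against.** The strongest reply is that no sentence puts session 1 in the wear week.

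- **The 12-week spacing is stated for controls.** The experimental arm is assessed before and after a 12-week programme, and visits that bracket such a programme can be more than 84 days apart. The 3-month wording also leaves room. This stands: a reader might infer that session 1 has to fall in the wear week, and the documents do not support that.
- **Even at 84 days, session 1 may fall on day 7**, with little overlap. This also stands.
- **A large first-week response is unlikely.** The Introduction stresses starting slowly and warns against abrupt increases, and accompanied walking begins only in session 2. This favours the low end of e, where the loss is small.
- **The reach is narrow.** Device sleep is little exposed because the sleep module starts in session 5, and the IPAQ is unaffected. This stands. The point is mainly about accelerometer activity.
- **Booking details belong in a fuller document, and 12 weeks and 3 months are near-synonyms.** This stands only in part. The article does not merely leave the timing open: it states a rule that wear follows the visit, and that rule, followed as written, admits on-treatment days. In most contexts the week between 84 and 91 days would not matter, but here it decides whether a full wear week fits before session 1.

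**Conclusion.** The point holds as a risk that the stated timing rule allows, with moderate confidence. The experimental arm's baseline device activity may include days after the exercise regimen has begun. If it does, and activity rises early, the activity contrasts at post-treatment, 6 months and 12 months are understated.

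A reader might go further and conclude that the baseline is on-treatment and the effect is biased toward zero. The documents do not support that. Overlap is not forced, and the direction depends on session 1 raising activity within days.

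The size cannot be derived from the document. For d = 0.70, 4 of 7 days overlapped and a week-1 response of 10–50% of the final one, d is about 0.66–0.50 and power 99–89%. At d = 0.89 power stays at 98% or more over the same range. Heavier overlap with a strong early response would cost more, but that combination fits poorly with a programme designed to start gradually. The likelier harm is an understated effect estimate rather than a failed test. It still merits a change, because a contaminated baseline cannot be collected again.

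**What to change.** 1. In the Accelerometry section, state that the baseline wear week is completed before the first health session, for example by booking session 1 at or after return of the watch.
2. For any participant whose wear week overlapped session 1, define the baseline device value as the valid wear days before that session. Use a matching window, counted from the baseline visit, in controls. Where session dates are recorded, this can also be applied to participants already enrolled.
3. Reconcile the 12-week wording in the Abstract with the 3-month wording under Outcome assessment sessions, and state one assessment interval for both arms that accommodates the wear week.

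**Cost:** a sentence or two and a booking rule, up to about one week's delay before session 1, and fewer baseline wear days for some participants under step 2. No extra visits or staff are needed.

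**Limit:** this does not remove any change in activity that comes from knowing the allocation. Randomization follows the phone contact and the trial is unblinded, so that is a separate matter.
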